## Abstract

**Background:**

Targeted analgesic dietary interventions are a promising strategy for alleviating pain and improving quality of life in patients with persistent pain syndromes, such as chronic daily headache (CDH). High intakes of the omega-6 (n-6) polyunsaturated fatty acids (PUFAs), linoleic acid (LA) and arachidonic acid (AA) may promote physical pain by increasing the abundance, and subsequent metabolism, of LA and AA in immune and nervous system tissues. Here we describe methodology for an ongoing randomized clinical trial comparing the metabolic and clinical effects of a low n-6, average n-3 PUFA diet, to the effects of a low n-6 plus high n-3 PUFA diet, in patients with CDH. Our primary aim is to determine if: A) both diets reduce n-6 PUFAs in plasma and erythrocyte lipid pools, compared to baseline; and B) the low n-6 plus high n-3 diet produces a greater decline in n-6 PUFAs, compared to the low n-6 diet alone. Secondary clinical outcomes include headache-specific quality-of-life, and headache frequency and intensity.

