Total polyunsaturated fatty acids (PUFA)	2.5	4.5
Linoleic acid, 18:2n-6 (LA)	<2.0	<2.0
Arachidonic acid, 20:4n-6 (AA)	60 mg	150 mg
Alpha-linolenic acid, 18:3n-3 (ALA)	0.6	1.8
Eicosapentaenoic acid, 20:5n-3 (EPA) + Docosahexaenoic acid, 22:6n-3 (DHA)	150 mg	1500-2000 mg

*All values are expressed as % of energy except AA and EPA+DHA (mg per day)

In this paper, we describe the design of the ongoing dietary trial, and report preliminary compliance data, as indicated by reductions in n-6 LA, AA and the percentage of n-6 highly unsaturated fatty acids (HUFA) in total HUFA (%n-6 in HUFA), and increases in EPA, DHA and omega-3 index in erythrocyte membranes. Implementation strategies are described along with methods for maintaining compliance and ensuring optimal data collection.

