### Outcome measures and study instruments

#### Primary Outcomes

The primary outcome (Aim 1) is the change in percentage of n-6 in HUFA in total HUFA (%n-6 in HUFA) in plasma and erythrocyte lipid pools, from pre-intervention (Week 6 - end of baseline phase) to post-intervention (Week 18). For determination of the %n-6 in HUFA, fatty acids that are at least 20 carbons in length with 3 more double bonds are considered to be HUFAs. The equation for calculation of %n-6 in HUFA is 100 × (20:3n-6 + 20:4n-6 + 22:4n-6 + 22:5n-6)/(20:5n-3 + 22:5n-3 + 22:6n-3 + 20:3n-6 + 20:4n-6 + 22:4n-6 + 22:5n-6 + 20:3n-9). For Aim 2, we examine the rate of change in %n-6 in HUFA over the 12 weeks of the intervention as measured at Study Week 6, Week 10, Week 14, and Week 18 (Weeks 0, 4, 8, and 12 of the intervention phase).

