#### Secondary Laboratory Outcomes

Secondary laboratory outcomes include individual n-6 and n-3 fatty acids in plasma and erythrocyte lipid pools, including n-6 linoleic acid (18:2n-6) and AA, as well as n-3 EPA and DHA. Lipid mediators derived from n-6 AA, EPA and DHA (e.g. eicosanoids, docosanoids), and mediators that may be indirectly influenced by n-6 and n-3 HUFA status (e.g. cytokines, pro-inflammatory enzymes, substance P), will be measured at study completion.

Changes in inflammatory gene expression in peripheral blood mononuclear cells (PBMCs) will be assessed in an additional pilot study. We will test: (1) the effects of the low n-6 diet compared to baseline dietary conditions (gene expression before the dietary intervention); (2) the effects of the low n-6 + high n-3 diet compared to baseline; and (3) the effects of the low n-6 versus the low n-6 + high n-3 diet compared to baseline. PBMCs are isolated from whole blood and RNA will be extracted utilizing Qiagen RNeasy Micro Kit (Valencia, CA). The RNA yield will be quantified with Nanodrop ND 1000 spectrophotometer (Nanodrop Technologies, Wilmington, DE), and integrity will be measured with an Agilent 2100 Bioanalyzer with RNA 6000 Nano chips (Santa Clara, CA). The expression of 84 key genes involved in the inflammatory response will be assessed using the Human Inflammatory Cytokines & Receptors RT² Profiler PCR Array (SA Biosciences, Frederick, MD).

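### The abstract states the primary aim as a decline in n-6 PUFAs, but the primary outcome is the n-6 share of HUFA, which excludes LA and also falls when n-3 rises

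*Protocol article*

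**What the plan says.** **The aim.** The abstract's primary aim has two parts. Part A is that both diets lower n-6 PUFAs relative to baseline. Part B is that "the low n-6 plus high n-3 diet produces a greater decline in n-6 PUFAs, compared to the low n-6 diet alone". The same paragraph says which n-6 PUFAs it means: "High intakes of the omega-6 (n-6) polyunsaturated fatty acids (PUFAs), linoleic acid (LA) and arachidonic acid (AA").

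**The primary outcome.** Under Primary Outcomes the article says: "The primary outcome (Aim 1) is the change in percentage of n-6 in HUFA in total HUFA (%n-6 in HUFA"), measured from Week 6 to Week 18. It adds that "fatty acids that are at least 20 carbons in length with 3 more double bonds are considered to be HUFAs". The formula begins "100 × (20:3n-6 + 20:4n-6 + 22:4n-6 + 22:5n-6)/(20:5n-3 + 22:5n-3 + 22:6n-3", and the rest of the denominator is the four n-6 HUFAs plus 20:3n-9. The analyses of Aim 1 and Aim 2 under Statistical Analysis both use this index.

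**LA and AA themselves.** These are secondary: "Secondary laboratory outcomes include individual n-6 and n-3 fatty acids in plasma and erythrocyte lipid pools".

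**The diets (Table 1).** The LA row reads "Linoleic acid, 18:2n-6 (LA) <2.0 <2.0", so the arms share that target. AA is 60 mg in the low n-6 arm and 150 mg in the low n-6 plus high n-3 arm. EPA+DHA is 150 mg and 1500-2000 mg respectively.

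**The concern.** The stated aim concerns how much n-6 is present. The index measures how HUFA divides between n-6 and everything else. The two differ in two ways:

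- LA, one of the two n-6 fatty acids the abstract names, has 18 carbons and 2 double bonds. It fails the HUFA definition, so no change in LA can move the index directly.
- The n-3 HUFAs are in the denominator. Raising them lowers the index even if every n-6 fatty acid stays where it was.

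Both arms are asked to restrict n-6. What separates them is chiefly n-3, and neither n-6 target is lower in the high n-3 arm. A positive between-arm result on the index could therefore be reported, in the abstract's wording, as a greater n-6 decline when only n-3 differed. What is at stake is the sentence the trial may write about its primary aim.

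**Working it through.** **Inputs (Table 5, erythrocytes, both arms pooled, n = 20 at baseline and 18 at Week 12).**

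| | Baseline | Week 12 | Change |
|---|---|---|---|
| %n-6 in HUFA | 76.3 | 64.7 | -11.6 points |
| AA | 14.8 | 13.7 | -1.1 (-7.4%) |
| EPA + DHA | 0.46 + 4.0 = 4.46 | 1.4 + 6.3 = 7.70 | +3.24 (+73%) |
| LA | 11.5 | 9.5 | -2.0 (-17%) |

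**Step 1: can the index be approximated from the tabulated values?** Table 5 omits the other HUFAs, so take AA/(AA + EPA + DHA) as a proxy.

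- Baseline: 14.8/(14.8 + 4.46) = 76.8, against 76.3 reported.
- Week 12: 13.7/(13.7 + 7.70) = 64.0, against 64.7 reported.

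The proxy is close. Now move one component at a time:

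- Only EPA+DHA changes: 14.8/(14.8 + 7.70) = 65.8, a fall of about 11 points.
- Only AA changes: 13.7/(13.7 + 4.46) = 75.4, a fall of about 1.4 points.

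**Step 2: calibrate to the reported index.** Assume 22:5n-3 (D) is constant between 0.5 and 3.0 and 20:3n-9 is negligible. The article gives neither value. Then total n-6 HUFA at baseline is (0.763/0.237) × (4.46 + D).

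| | D = 0.5 | D = 3.0 |
|---|---|---|
| Baseline n-6 HUFA | 3.219 × 4.96 = 16.0 | 3.219 × 7.46 = 24.0 |
| Index if only n-3 rises | 16.0/(16.0 + 8.20) = 66.1 | 24.0/(24.0 + 10.70) = 69.2 |
| Share of the 11.6-point fall | (76.3 - 66.1)/11.6 = 88% | (76.3 - 69.2)/11.6 = 61% |
| Index if only AA falls by 1.1 | 14.9/(14.9 + 4.96) = 75.0 | 22.9/(22.9 + 7.46) = 75.4 |

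**Step 3: allow for all n-6 HUFAs, not only AA.** Under the same assumptions, the Week 12 index of 64.7 implies n-6 HUFA of (0.647/0.353) × (7.70 + D).

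- D = 0.5: 1.833 × 8.20 = 15.0, a 6% fall from 16.0. This fall alone gives 15.0/(15.0 + 4.96) = 75.2, or 1.1 points.
- D = 3.0: 1.833 × 10.70 = 19.6, an 18% fall from 24.0. This fall alone gives 19.6/(19.6 + 7.46) = 72.4, or 3.9 points.

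Across the range, the n-3 rise moves the index more than the n-6 fall does. At the upper end, though, AA alone understates the n-6 fall about fourfold (24.0 - 19.6 = 4.4, against 1.1).

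**Step 4: the contrast between arms.** Table 1 gives equal LA targets, AA of 150 against 60 mg, and EPA+DHA of 1500/150 = 10 to 2000/150 = 13.3 times as much in the high n-3 arm. No n-6 target favours a larger n-6 fall in that arm. The n-3 target directly favours a larger fall in the index.

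**The case against.** Several points on the other side stand.

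- The body of the article already frames the analysed aims on the index. Primary Outcomes, the analyses of Aims 1 and 2, and the closing paragraph of Results all do so, and the formula is printed twice. An analyst following the Methods would test and report the right quantity. The mismatch lies in the abstract's statement of the aim.
- The index suits the hypothesis. The Role of Diet in Chronic Pain section describes n-3 and n-6 HUFAs as competitors, so sensitivity to n-3 is intended. It is a defensible primary biomarker.
- n-6 HUFA, including AA, is in the numerator, so a real n-6 fall also lowers the index. Because the denominator includes 20:3n-9, it is not strictly an n-6/n-3 ratio.
- AA and LA are prespecified secondary outcomes. The Discussion's first open question asks about them directly, and the Discussion cautions that the pooled data cannot show whether AA and the index fell in both diet groups.

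A reader might go further and infer that the index cannot inform the aim at all, that part B will be confirmed almost automatically, or that AA will fall less in the high n-3 arm. The documents do not support these readings. The first ignores the numerator. The second needs between-arm data, and Table 5 pools the arms. The third treats intake targets as tissue levels, although the article says tissue AA also depends on LA and on competing EPA and DHA.

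None of this removes the mismatch. The published primary aim still promises a conclusion about n-6 PUFAs that the primary test alone cannot deliver.

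**Conclusion.** The point holds as a mismatch between the abstract's primary aim and the primary outcome. On its own the index cannot tell an n-6 decline from an n-3 rise, and it does not contain LA. Given Table 1, a between-arm difference could come from n-3 intake alone.

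The sensitivity is large: 61% to 88% of the pooled fall in the index is reproduced by the n-3 rise with n-6 held still. That range depends on the assumed 22:5n-3 of 0.5 to 3.0 held constant, negligible 20:3n-9, and erythrocyte means from about 20 participants with the arms combined. It illustrates how the index behaves and is not an estimate for part B. That the index is insensitive to LA, and that n-3 lowers it, follows from the formula and needs none of these assumptions.

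This should be corrected because it determines what the trial may conclude. It does not invalidate the primary outcome.

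**What to change.** 1. Keep %n-6 in HUFA as the primary outcome.
2. Reword parts A and B of the abstract's aim as effects on the n-6 share of HUFA, in line with Primary Outcomes and the analyses of Aims 1 and 2.
3. Analyse the already prespecified AA and LA, in both plasma and erythrocytes, with the same baseline-adjusted between-arm model as the index.
4. State that n-6 PUFAs, or AA or LA specifically, declined or declined more only for the fatty acid and pool in which this is shown. A result for one fatty acid should not carry a general n-6 claim.

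How multiplicity across these comparisons is handled can be left to the statistical analysis plan, which is not shown.

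The cost is a change of wording and a few analyses of fatty acids that are assayed anyway. The drawback is that the permitted conclusion may be less favourable: the index could differ between arms while AA and LA do not.

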**Methods:**

Adults meeting the International Classification of Headache Disorders criteria for CDH are included. After a 6-week baseline phase, participants are randomized to a low n-6 diet, or a low n-6 plus high n-3 diet, for 12 weeks. Foods meeting nutrient intake targets are provided for 2 meals and 2 snacks per day. A research dietitian provides intensive dietary counseling at 2-week intervals. Web-based intervention materials complement dietitian advice. Blood and clinical outcome data are collected every 4 weeks.

**Results:**

Subject recruitment and retention has been excellent; 35 of 40 randomized participants completed the 12-week intervention. Preliminary blinded analysis of composite data from the first 20 participants found significant reductions in erythrocyte n-6 LA, AA and %n-6 in HUFA, and increases in n-3 EPA, DHA and the omega-3 index, indicating adherence.

**Trial Registration:**

ClinicalTrials.gov (NCT01157208)

## Background

Targeted analgesic dietary interventions are a novel strategic approach with promise for alleviating pain and improving quality of life in patients with persistent pain syndromes. Chronic Daily Headache (CDH), defined as presence of headaches lasting 4 hours or more for 15 or more days per month over at least 3 months, is a debilitating pain syndrome that affects 4 to 5% of the adult population in the US, roughly 10 million Americans [1-6]. Loss of work and medical expenses add up to billions of dollars per year [7,8]. Chronic episodic migraines, chronic tension-type headaches, and other primary headaches may evolve into CDH, which is believed to represent a final common pathway for several distinct headache types [9,10]. CDH accounts for up to 40% of patients presenting to headache specialty clinics. Patients with CDH often receive only limited benefit from conventional medical management. Conventional treatments rely heavily on medications that may provide limited or transient relief, target symptoms rather than underlying causes of pain, and are associated with significant side effects and costs [11-15]. Paradoxically, headache medications may facilitate the transformation of intermittent headaches to more frequent and disabling chronic daily headaches [16]. Moreover, medication side effects are often significant and include not only medication overuse syndromes, but also weight gain, fatigue, and depression, among many other side effects [12,13].

### The Role of Diet in Chronic Pain

Multiple metabolic pathways that are important in pain processing converge at the level of omega-6 (n-6) arachidonic acid (AA) metabolism. AA can directly potentiate N-methyl-d-aspartate (NMDA) receptor currents [17-19]. AA is also the precursor to a wide array of neuroactive [20-23] and vasoactive [24-27] compounds that are relevant to pain processing. We hypothesized that the overabundance and/or hyperactive metabolism of n-6 AA in nervous and immune system tissues serve as a fundamental metabolic basis for central pain sensitization and human physical pain [28].

Certain dietary patterns may promote physical pain by increasing the amount and/or subsequent metabolism of AA in nervous and immune system tissues [28]. Humans cannot synthesize AA *de novo*. Tissue phospholipid concentrations of AA (PL-AA) are dependent on dietary intake of 1) n-6 AA [29]; 2) a precursor to AA, linoleic acid (LA) [30]; and 3) competing fatty acids, including n-3 eicosapentaenoic acid (EPA) and docosahexaenoic acid (DHA) [31]. Competition continues as n-6 AA and n-3 EPA + DHA act as rival substrates for enzymatic cleavage and conversion into bioactive compounds (e.g. eicosanoids, docosanoids, endocannabinoids, and endovanilloids). Thus, restricted n-6 consumption and/or increased intake of competing fatty acids may diminish the consequences of elevated tissue concentrations of AA and/or the synthesis of AA metabolites. Restricted n-6 consumption and/or increased n-3 EPA + DHA intake may also increase the abundance and subsequent metabolism of EPA and DHA derivatives with analgesic properties (e.g. resolvins, neuroprotectins) [32].

To test this hypothesis, we designed a 12-week, controlled dietary trial in 76 participants with CDH randomized into 1 of 2 arms: 1) usual medical care plus a low n-6 diet with <2.0 percent of energy (en%) as linoleic acid (LA), <60 mg/d of AA, and average US n-3 intake (Table 1); or 2) usual medical care plus a low n-6, high n-3 diet with <2.0 en% as LA, 1.8 en% as alpha-linolenic acid (ALA) and >1.5 g/d of EPA+DHA (Table 1).

**Table 1 T1:** Nutrient intake targets for a study of exploratory analgesic dietary interventions for chronic daily headache, May 2010*

Nutrient	Low omega-6 diet	Low omega-6 + High omega-3 diet
Total protein	18	18
Total carbohydrate	50	50
Total fat	32	32
Trans fatty acids	<0.5	<0.5
Total saturated fat	13	13
Total monounsaturated fatty acids (MUFA)	16	14
Total polyunsaturated fatty acids (PUFA)	2.5	4.5
Linoleic acid, 18:2n-6 (LA)	<2.0	<2.0
Arachidonic acid, 20:4n-6 (AA)	60 mg	150 mg
Alpha-linolenic acid, 18:3n-3 (ALA)	0.6	1.8
Eicosapentaenoic acid, 20:5n-3 (EPA) + Docosahexaenoic acid, 22:6n-3 (DHA)	150 mg	1500-2000 mg

*All values are expressed as % of energy except AA and EPA+DHA (mg per day)

In this paper, we describe the design of the ongoing dietary trial, and report preliminary compliance data, as indicated by reductions in n-6 LA, AA and the percentage of n-6 highly unsaturated fatty acids (HUFA) in total HUFA (%n-6 in HUFA), and increases in EPA, DHA and omega-3 index in erythrocyte membranes. Implementation strategies are described along with methods for maintaining compliance and ensuring optimal data collection.

## Methods

### Study Design

The study is a randomized trial comparing 2 dietary interventions designed to reduce tissue content of AA and total n-6 HUFA, and testing the impact of these interventions on alteration of the phenotypic expression of CDH. Figure 1 illustrates the overall design and subject flow through the study. Study procedures and consent forms were reviewed and approved by the Institutional Review Board and the Clinical and Translational Research Center (CTRC) of the University of North Carolina (UNC).

**Figure 1 F1:**
[figure not shown]
**Study flow diagram for the exploratory analgesic dietary intervention for chronic daily headache, May 2010**. Abbreviations: HUFA, highly-unsaturated fatty acid; HIT-6, Headache Impact Test; MIDAS, Migraine Disability Assessment Questionnaire; BSI-18, Brief Symptom Inventory.

### Eligibility

Patients referred to the study are screened for CDH using the 2004 International Classification of Headache Disorders (ICHD-II) criteria, and are evaluated for eligibility using the inclusion and exclusion criteria listed in Table 2. Our target is 76 participants qualifying for randomization. Based on our experience with attrition rates in headache studies, we expect at least 80% of the headache sufferers enrolled in the trial to complete the intervention.

**Table 2 T2:** Eligibility of subjects for participation in the study of dietary interventions for chronic daily headache, May 2010

All subjects are evaluated by a neurologist prior to enrollment	
**Inclusion Criteria**	**Exclusion Criteria**

• Subjects >18 years of age	• Marked depression, anxiety or psychosis
• Either gender • Meets 2004 ICHD-II* criteria for Chronic Daily Headache • Headache frequency days/month: > 15 • Headache history: > 2 years Includes: Chronic migraine, transformed episodic migraine into CDH, chronic tension-type headache and persistent daily headache • Willing to complete daily diary for 6 weeks • Able to attend 12 weekly treatments • Under care of physician for headaches • Able to read and communicate in English	• Pregnancy or anticipated pregnancy • Active treatment for a major medical illness, such as malignancy, autoimmune or immune deficiency disorder • History of significant head trauma or head/neck surgery within the past 2 years • History of subarachnoid or intra-cerebral hemorrhage or chronic subdural hematoma • History of clotting disorder • History of systemic infection such as meningitis or encephalitis • History of vasculitis or intracranial mass • Cognitive dysfunction that would prevent informed consent

*International Classification of Headache Disorders, defined by expert members of the International Headache Society

### Recruitment

Participants are recruited from the following sources: 1) University of North Carolina (UNC) Headache Clinic; 2) multiple area neurology practices; 3) broadcast email to UNC employees and students; 4) brochures and flyers at UNC clinics and research centers.

### Screening, consent, and enrollment procedures

Interested individuals contact the research staff for a telephone screening interview. If the screening process identifies them as potentially eligible, the individuals meet with the study staff for consenting, a baseline neurological assessment, and completion of baseline measures. The study neurologist confirms the diagnosis of CDH and excludes from the study those individuals with other medical problems that could put the participant at risk or confound the study results. Individuals may also be excluded if they are unwilling or unable to commit to a 12-week dietary intervention. Excluded patients are referred back to their physicians for further medical management. Enrolled participants continue to be cared for by their personal physicians, but are asked to avoid changes in over-the-counter medications, dietary supplements, and non-pharmacologic treatments for headache during the course of the study. Medication changes for headache management by the treating physician are allowed and documented.

### Baseline Period

Eligible participants are instructed in the maintenance of a daily online headache diary for 6 consecutive weeks while continuing usual care. After they have completed 4 weeks of diaries, their entries are reviewed with the study neurologist to determine eligibility for the treatment phase of the study. Eligibility consists of completion of at least 80% of headache diaries and report of at least 15 headache days per month. Each headache day must have a minimum of 4 consecutive hours of headache. Eligible participants are scheduled to visit the research dietitian for 7 consultations over the course of the 12-week intervention. They are asked to continue their headache diaries for the full 18-week duration of the study.

### Randomization

At the first treatment visit, study participants are randomized to 1 of 2 diets, a low n-6 diet, or a low n-6 plus high n-3 diet (Figure 1 and Table 1), to be maintained for 12 consecutive weeks. Randomization employs a computer algorithm using a random number sequence to generate a permuted block of 4-8 subjects, ensuring equal numbers of participants in each arm of the study [33]. The program, accessed only through an on-line interface by the study dietitian, also documents treatment assignment in an un-editable form with a date stamp.

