### Masking

Because of the nature of the interventions, the research dietitian cannot be masked to treatment condition. Similarly, participants are aware of the foods included in their diets. However, participants do not have access to information about the other diet. In addition, steps are taken to ensure that credibility of both dietary interventions is maintained. A questionnaire assessing the credibility of both diets as an intervention for headache is administered after the first visit with the dietitian. All investigators except the research dietitian are masked to treatment assignment. Similarly, participants' personal physicians are masked to treatment assignment.

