## Results

Recruitment into the study has proceeded as planned (Table 4). The majority of participants have been referred by their health care provider, particularly those who see a neurologist. Other participants are self-referred, having learned about the study through UNC advertisements, brochures, flyers, friends and family.

**Table 4 T4:** Recruitment for the exploratory analgesic dietary intervention for chronic daily headache, May 2010

	N	Percent
Inquiries about study	183	
Potentials to be screened	59	32.2
Screened	124	67.8
Eligible, but declined to participate	5	4.0
Ineligible at telephone screen	35	28.2
Headache characteristics	15	42.9
Medical/psychiatric problems	4	11.4
Logistic problems (time/distance)	11	31.4
Dietary Issues	2	5.7
Other/unknown	3	8.6
Scheduled for baseline consent	84	68.3
Ineligible at baseline consent	5	6.0
Eligible at baseline consent	79	94.0
Withdrew/ineligible before randomization	10	11.9
Withdrew after randomization	5	6.0
Awaiting baseline visit	18	14.5
Enrolled	46	37.9
Referral pattern		
Health professionals*	126	72.0
Electronic advertisements	32	18.3
Print advertisements	12	6.9
Family/Friends	2	1.1
Prior Study	3	1.7
Unknown	8	

* Health professionals that referred patients to the study included neurologists, family physicians, and nurses.

At this time, 124 individuals have been screened for eligibility of which 63 were enrolled into the study. Five enrolled individuals were ineligible to begin the dietary intervention due to low headache frequency (3), an intervening illness (1), or failure to keep up with the diaries. In addition to those who did not qualify, 10 individuals withdrew after giving consent, 5 during the baseline phase and 5 during the diet phase. Of the 5 individuals who withdrew during the baseline phase, 4 cited scheduling difficulties and 1 moved out of town. Of the 5 individuals who withdrew after randomization, 3 cited difficulty adjusting to the diet, 1 became pregnant, and another withdrew due to a traumatic injury that was unrelated to the study diet.

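### The only unmasked investigator is also the sole operator of the randomisation program, and with blocks of 4-8 can guess the next diet about two times in three; a masked colleague should enter the participant instead.

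*Protocol article*

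**What the plan says.** All references are to the protocol article.

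- **Randomization.** Assignment takes place at the first treatment visit. The algorithm uses "a permuted block of 4-8 subjects, ensuring equal numbers of participants in each arm of the study". On access: "The program, accessed only through an on-line interface by the study dietitian". The program "also documents treatment assignment in an un-editable form with a date stamp".
- **Masking.** Here "the research dietitian cannot be masked to treatment condition". Every other investigator is masked, and so are the participants' own physicians.
- **Interventions.** Both arms see the dietitian roughly every two weeks at one research centre.
- **Baseline Period.** Eligibility for the treatment phase is settled in a diary review with the study neurologist after four weeks of diaries. The criteria are countable: diary completion of at least 80% and at least 15 headache days per month. Then: "Eligible participants are scheduled to visit the research dietitian for 7 consultations over the course of the 12-week intervention". Who does the scheduling is not stated.
- **Interventions and Outcome measures.** Baseline blood is drawn at the first intervention visit (Week 6), which is also the visit at which the participant is randomised.

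**The concern.** Allocation concealment requires that whoever triggers a participant's assignment cannot foresee it. Here that task is given to the one investigator who knows what has gone before, in a scheme whose short blocks make the history informative. The un-editable, date-stamped record prevents changes after the draw. It does nothing about anticipation before the draw.

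What could be affected is who is drawn when. A first visit might be moved, two visits might change order, or a hesitant participant might be lost at the last moment, in the light of the diet expected next. The diets differ visibly (daily fatty fish and flaxseed in one arm only). Willingness to follow the diet also matters for retention: under Results, three of the five withdrawals after randomisation cited difficulty adjusting to it. The Aim 1 regression adjusts for the baseline proportion, age, sex and BMI, none of which measures willingness. The primary outcome is a laboratory value, so the issue is comparability of the arms at entry, not biased assessment. Adherence does, however, drive that value.

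**Working it through.** The article gives no predictability figure, so there is none to reproduce.

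**Inputs from the article.** Two arms in equal numbers and blocks of 4-8 (Randomization); 76 participants (Eligibility); one operator who knows past assignments (inferred from Randomization, Masking and Interventions together).

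**Assumptions.** The study dietitian and the research dietitian are the same role. Block sizes are even, so 4, 6 or 8. Where sizes vary, they are drawn with equal probability.

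**Step 1: known block size.** The guesser names the arm with fewer assignments so far and tosses a coin when the arms are level. For a block of size 2k the expected share of correct guesses is

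[k + 2^(2k-1)/C(2k,k) - 1/2] / (2k)

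- Size 4: (2 + 8/6 - 0.5)/4 = 2.833/4 = 70.8%
- Size 6: (3 + 32/20 - 0.5)/6 = 4.1/6 = 68.3%
- Size 8: (4 + 128/70 - 0.5)/8 = 5.329/8 = 66.6%

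**Step 2: sizes varying at random and boundaries unknown.** Simulation with 76 participants and sizes 4, 6 and 8 gives 67.9% with the same simple rule (20,000 trials). A guesser who makes best use of the history also gets 67.9% (3,000 trials). Varying the size therefore does not lower the average guess rate below that of a fixed block of 8.

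**Step 3: assignments known with certainty.** This is where varying the size helps.

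| Scheme | Certain assignments |
|---|---|
| Fixed and known, size 4 | 33% |
| Fixed and known, size 6 | 25% |
| Fixed and known, size 8 | 20% |
| Random over 4 and 8 | about 7% |
| Random over 4, 6 and 8 | about 2% |

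**Step 4: guessing ahead.** A visit is usually booked before the preceding draws are all known. With sizes 4, 6 and 8, the rate falls to about 60% one draw ahead, 56% two ahead and 53% three ahead.

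**Step 5: stratification.** The article mentions no strata, but a condensed article may omit them. Four equal strata (assumed) still give 66.6%, so the result does not depend on this.

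**Step 6: what a guess rate could do.** Suppose that every participant could be steered, with an expected outcome shifted by +h or -h according to the predicted arm. The arms would then differ by 2h(2p - 1), where p is the guess rate:

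- p = 0.68: 2h × 0.36 = 0.72h
- p = 0.60: 2h × 0.20 = 0.40h

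These are ceilings under complete steering. The article gives no value for h and no share of entries that could be steered, so they do not estimate the bias.

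**The case against.** The strongest objection is that guessing is not steering, and that the article describes no route from one to the other. Research staff do the telephone screening and study staff take consent. Eligibility is reviewed with the study neurologist, who as an investigator is masked, on countable criteria. Entry is tied to the end of a six-week diary, so order follows largely from the date of consent. Nothing gives the dietitian control of booking or exclusion. Accrual is also thin: 76 participants in about 30 months is 76/30 = 2.5 per month, or little more than one per fortnight, so there is rarely a second participant to exchange. The primary outcome is a laboratory measure, and the clinical outcomes are declared not to be powered.

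Most of this stands, and it sets the limits of the point. Three stronger readings are tempting, and the article supports none of them:

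- **That the dietitian can choose who enters the trial.** Participants have already consented and been found eligible. Only the draw remains.
- **That the arms are biased by about 0.7h.** That requires every entry to be steerable and every guess to be made at the moment of the draw.
- **That the baseline losses show steering.** Results states: "Of the 5 individuals who withdrew during the baseline phase, 4 cited scheduling difficulties and 1 moved out of town". These are participants' own reasons, and nothing links them to a predicted diet.

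What the objection does not remove is the allocation of tasks itself. It is stated in the article, not inferred from an omission. Between the neurologist's review and the first treatment visit, no stated step fixes a participant's place in the sequence. The article also allows exclusion of people unwilling or unable to commit, without saying who decides.

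**Conclusion.** The point holds as a limited weakness in allocation concealment. The one unmasked investigator operates the program alone and can guess the immediate next assignment about 66-71% of the time, or about 60% one draw earlier. If sizes vary at random over 4, 6 and 8, about 2% of assignments are certain. The exposure is confined to the timing, order or last-minute loss of entries at the first treatment visit.

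There is no evidence that steering occurred, and the size of any bias is unknown. The conclusion rests on reading the two dietitian titles as one role and on that person knowing the earlier assignments. It does not depend on the exact block size or on the absence of strata. It does not invalidate the trial; it is worth acting on because the remedy costs almost nothing.

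**What to change.** Apply the change to participants not yet randomised. The Abstract reports 40 randomised against a target of 76, so at most 76 - 40 = 36 entries could benefit.

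1. At the Week 6 visit, once eligibility is confirmed and the baseline blood and questionnaires are complete, an existing staff member who is masked to assignment enters the participant in the program.
2. The program locks that entry with a date stamp before the participant has contact with the dietitian.
3. The assignment is then shown only to the dietitian, so the person who made the entry stays masked.
4. The protocol states that block sizes vary at random and are not disclosed to the dietitian. This mainly removes certain guesses. The separation of tasks in steps 1 to 3 is what removes the exposure.

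Entry should not be moved forward to the four-week diary review and counted as randomisation. Losses between that review and Week 6 would then join the intention-to-treat population without a baseline blood sample.

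The cost is a change of user rights in the existing program, a few sentences in the protocol and a small scheduling step at that visit. No diet, sample size or clinical rule changes.
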